### Study Cohort

Patients eligible for percutaneous ablation will be randomized prior to the procedure into one of two study arms: percutaneous MWA (arm A) or SBRT (arm B). Patients with at least one additional CRLM requiring resection will undergo laparoscopy or laparotomy with surgical inspection of the abdominal cavity and intraoperative ultrasound (IOUS) and if still considered eligible randomized intraoperatively. If randomized to MWA during open laparotomy, the eligible tumours will be ablated in the same procedure using ultrasound guidance. Patients included in study arm B will undergo SBRT at a later time. SBRT will be planned as soon as the patient is recovered from surgery. Patients randomized prior to treatment will have to be treated within 4 weeks after randomization.

### Randomization

Blocked randomization with randomly selected block sizes of 4 and 6 will be performed centrally through a web-based module (CASTOR), with stratification according to presence of extrahepatic disease and patients undergoing surgical resection. According to the intention-to-treat concept, during statistical analysis all randomized patients will be analysed in the group they were originally assigned to even when receiving a different treatment.

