Participants will be stratified according to presence of extrahepatic disease and whether patients will undergo surgical resection. An experienced expert panel, consisting of at least two interventional radiologists, two hepatobiliary surgeons and two radiation oncologists, will determine whether the CRLM are (un)resectable and/or (un)ablatable. Unresectable intermediate-size CRLM suitable for both MWA and SBRT are so-called target-tumours. All additional non-target tumours should be resectable or, if unresectable and ≤ 3 cm, eligible for thermal ablation.

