### Statistics

Given the unknown 1 year LTP rate for intermediate-size CRLM for both techniques, it was not possible to apply validated assumptions for both proportions. Hence a difference in 1y-LTP rate of more than one third (33%) is considered clinically relevant as it seems unlikely that a smaller difference will significantly impact overall survival. Most 1-year LTP will either be re-ablated or patients will receive systemic chemotherapy because of the simultaneous presence of extensive distant progression. In other words, unablatable LTP at 1-year without recurrence at distant sites is uncommon. We therefore accept that a difference in 1 year LTPFS of more than one third (0.33) will reject the null hypothesis concluding that the techniques are significantly different [17]. Group sample sizes of 33 in group 1 and 33 in group 2 achieve 81.059% power to detect a difference between the group proportions of −0.33. The proportion in group 1 (the treatment group) is assumed to be 0.665 under the null hypothesis and 0.3350 under the alternative hypothesis. The proportion in group 2 (the alternative treatment group) is 0.665. The test statistic used is the two-sided Z-test with un-pooled variance. The significance level of the test is 0.05. To account for a 3% loss to follow-up (= 2 patients) we need to randomize 34 patients (NR) into each of the two arms.

Baseline patient-, tumour- and treatment characteristics will be described and compared between the two treatment arms using the Chi-square test for categorical variables and the independent two-sample t-test, ANOVA or Mann–Whitney-U-test for continuous variables. *P* values below 0.05 will be considered significant. When appropriate, box-plots and cross-tables will be used for descriptive statistics of continuous and categorical variables, respectively. One year LTPFS rates will be compared between MWA and SBRT using the Chi square test. To determine hazard ratios (HR) for multivariate analysis, logistic regression will be used. Univariate LTPFS time analysis will be performed using the Kaplan–Meier method with corresponding two sided 95% confidence intervals (CI). Differences in LTPFS length will be analysed using the log rank test.

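### Randomisation is stratified by extrahepatic disease and surgical resection, but the named chi-square and log-rank tests use neither factor, which gives up some power if the factors predict local progression

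*Protocol article*

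**What the plan says.** The Inclusion Criteria section states: "Participants will be stratified according to presence of extrahepatic disease and whether patients will undergo surgical resection". The Randomization section repeats the two factors, "with stratification according to presence of extrahepatic disease and patients undergoing surgical resection", and adds the mechanism: "Blocked randomization with randomly selected block sizes of 4 and 6", allocated centrally. Two binary factors give four strata.

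The Statistics section fixes the analysis. For the primary endpoint: "One year LTPFS rates will be compared between MWA and SBRT using the Chi square test". For time to event: "Univariate LTPFS time analysis will be performed using the Kaplan–Meier method", and "Differences in LTPFS length will be analysed using the log rank test". Neither test is described as stratified or adjusted. One adjusted analysis is mentioned: "To determine hazard ratios (HR) for multivariate analysis, logistic regression will be used". Its covariates are not named, and it is not given as the test of the primary endpoint. The sample size rests on an unstratified two-sided Z-test with un-pooled variance, 33 per arm, rates 0.335 and 0.665. For alpha: "The significance level of the test is 0.05".

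**The concern.** Blocking within strata forces the arms to be alike on the two factors. If a factor predicts outcome, the treatment difference varies less from one hypothetical trial to the next than it would under simple randomisation. A chi-square or log-rank test that ignores the strata still uses the larger variance of simple randomisation. Its standard error is then too large for the design, the test rejects too seldom under the null, and some power is lost.

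The factors could matter here. The sponsor chose them for balancing, and the Study Cohort section shows that surgical patients follow another pathway: they are randomised during the operation, microwave ablation takes place in the same session if the abdomen is open, and radiotherapy waits for recovery. In a trial of 68 patients planned at about 81% power there is little to spare, and both factors are already recorded at randomisation.

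**Working it through.** **1. The plan's own power figure.** Inputs from the Statistics section: 33 per arm, rates 0.335 and 0.665, two-sided alpha 0.05, un-pooled variance.

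- SE = √(0.335 × 0.665/33 + 0.665 × 0.335/33) = √0.0135 = 0.1162
- Power = Φ(0.33/0.1162 − 1.96) = Φ(0.880) = 0.8106

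This reproduces the stated 81.059%. The figure belongs to an unstratified test, so sizing and analysis agree with each other. The mismatch is between the analysis and the randomisation. The pooled-variance approximation, which is closer to a chi-square test, gives 77.7%. The exact binomial power of the uncorrected test is 81.3%.

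**2. What the article does not give.** It states neither how common each factor is nor how strongly it predicts local progression. Both must be assumed.

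**3. Simulation.** Four strata, permuted blocks of 4 and 6, independent patients, marginal rates 0.665 v 0.335 for power and 0.665 in both arms for alpha. The uncorrected chi-square is compared with a Cochran-Mantel-Haenszel (CMH) test over the four strata. Each factor is assumed present in 30%, with the same odds ratio (OR) for both.

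| Patients | OR per factor | Power, chi-square | Power, CMH | CMH gain (points) |
|---|---|---|---|---|
| 66 | 1 | 79.3% | 77.0% | −2.3 |
| 66 | 2.7 | 80.6% | 81.4% | 0.8 |
| 66 | 4.5 | – | – | about 3 |
| 68 | 1 | 77.8% | 78.0% | 0.2 |
| 68 | 2.7 | 77.8% | 81.5% | 3.7 |
| 68 | 4.5 | 78.8% | 84.6% | 5.8 |

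Repeat runs at 66 patients and OR 2.7 put the gain at about 0.5 to 1 point. At 68 patients and a null rate of 0.665, the chi-square type I error is about 4.1 to 4.7% at OR 2.7 and about 3.2 to 4.1% at OR 4.5. It is lower (3.6 to 3.8% and 2.8 to 3.2%) only at a null rate of 0.5, which the protocol does not use.

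Part of the jump between 66 and 68 is discreteness of the chi-square test: with inert factors its power is lower at 68 (77.8%) than at 66 (79.3%).

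**4. Wider range.** At 66 patients, with prevalences of 20%/30% or 40%/40% and ORs below 1 (8,000 runs per setting; Monte Carlo SE about 0.24 points for alpha, 0.45 for power):

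| OR per factor | Alpha, chi-square | Alpha, CMH | Power, chi-square | Power, CMH |
|---|---|---|---|---|
| 1 | 5.1–5.8% | 4.6–5.5% | 78.5–80.2% | 76.6–77.9% |
| 0.5 | 4.6–4.7% | 4.7–4.9% | 79.4–80.0% | 78.6–79.5% |
| 0.33 | 3.8–4.6% | 4.7–5.1% | 80.1–80.8% | 81.6–82.1% |
| 0.2 | 3.4–3.5% | 5.0–5.1% | 81.3% | 84.2–85.7% |
| 0.1 | 1.9–2.3% | 4.8–5.1% | 82.4–83.5% | 88.8–91.1% |

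The stratified test begins to pay at an OR of roughly 2 to 3 per factor, in either direction.

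**5. The opposing force.** The Outcome Measures section counts the endpoint per treated tumour, and a patient may have one to three target tumours. Assume 1.5 tumours per patient and an intra-patient correlation (ICC) of 0.1 to 0.5. The design effect is 1 + (1.5 − 1) × ICC = 1.05 to 1.25. A test that ignores it has alpha = 2 × [1 − Φ(1.96/√DE)], about 5.6% at 1.05 and 8.0% at 1.25.

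**The case against.** The strongest reply is that the harm is conditional. The endpoint is local eradication of the target tumours. Resection concerns additional tumours, and extrahepatic disease lies outside the liver, so neither factor need predict local progression strongly. With weak factors the stratified test gains nothing, and at 66 patients it can be about 2 points weaker. This stands, and it limits the size of the point.

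A second reply is that the planned chi-square delivers about 78 to 84% power in every scenario examined, so the trial is not underpowered through this choice. That also stands.

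A third is that adjustment is partly planned and its detail belongs to an analysis plan that is not shown. This stands only in part. The logistic regression may include the two factors, but the article does not make it the primary test. It does name the primary test and the log-rank test, and describes neither as stratified. That is a stated choice rather than an omitted detail.

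A reader might infer that the trial's type I error is simply too low, or that stratifying is precision for free. The article supports neither. The first overlooks the per-tumour endpoint, where unmodelled clustering raises alpha, so the net direction is unknown. The second fails when the factors are inert.

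**Conclusion.** The mismatch between a stratified randomisation and unstratified tests is in the text and holds. Its cost is modest and depends on unstated prognostic strength. With each factor in 30% of patients and ORs of 2.7 to 4.5, the unstratified chi-square gives up about 0.5 to 3 points of power at the planned 66 evaluable patients and about 4 to 6 points if all 68 are evaluable. Its alpha is then about 3 to 5%, counting the stratification alone. With inert factors the sign reverses, by about 2 points at 66 patients. These sizes come from simulating the 1-year binary comparison with independent patients. The log-rank test was not simulated; the same reasoning applies to it in direction only. The change is worth making because the possible gain exceeds the possible loss and the analysis would then follow the design. It does not undermine the trial's stated power.

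**What to change.** Name a primary 1-year comparison that accounts for both stratification factors. One option is a CMH stratified risk difference. The other is a model with both factors as covariates that also handles tumours clustered within patients. While the endpoint stays per tumour the model is the safer choice, since a CMH analysis of tumours treated as independent would leave the clustering untouched. For LTPFS time, use a log-rank test or Cox model stratified by the two factors. Keep the unstratified chi-square and log-rank tests as sensitivity analyses.

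State in advance what happens to sparse strata: at 30% prevalence for each factor (assumed independent), the smallest holds about 0.3 × 0.3 × 66 ≈ 6 patients. Fix the choice before outcome data by arm are seen.

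The cost is wording in the analysis plan. Both factors are already held in the randomisation system, and no extra patients or data are needed. The price is the possible loss of about 2 points of power at 66 patients if the factors turn out not to be prognostic.

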### Microwave Ablation

MWA procedures will be performed by a board certified operator striving for a tumour free ablation margin of at least 1 cm, according to the CIRSE quality improvement guidelines [18]. Contra -indications for a percutaneous approach are proximity of critical structures that cannot be distanced using pneumo- or hydrodissections. The interventional radiologist will assess the necessity for overlapping re-ablations and needle repositioning. To assess technical efficacy a ceCT (or ceMRI) should be made within two weeks after the procedure. Completion ablations for residual disease or inadequate tumour-free safety margins are allowed if detected on cross-sectional imaging and retreated ≤ 6 weeks after initial treatment. In this case, the initial procedure will be evaluated as a technically unsuccessful procedure. However, when successfully re-ablated the retreated residue will not count as an event for the primary endpoint LTPFS. If successfully re-ablated within 6 months after the initial treatment, early ablation site recurrence will not be regarded as an event for the primary endpoint 1 year LTPFS. The use of either rigid and/or non-rigid confirmation software is considered mandatory aiming at a minimum of 5 mm margins.

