### Follow-Up

Follow-up imaging and laboratory tests will be identical in both treatment arms to avoid bias with regards to both the primary and secondary endpoints such as distant progression (Fig. 2). Patients will be asked to complete quality of life questionnaires at baseline and every 3 months for the first year. All potential LTPs will be reviewed by an expert panel including independent abdominal radiologists in presence of the study PI’s.

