## Discussion

Currently, guidelines state that thermal ablation can be applied for unresectable CRLM of limited-size (≤ 3 cm) and that SBRT should be considered if the location of the tumour is unfavourable for thermal ablation [19–21]. However, the preferred treatment option for intermediate-size unresectable CRLM (3-5 cm) has not been established. Following both thermal ablation and SBRT, LTP rates increase with larger tumour size [17, 22–28]. Patients eligible for both treatment options often receive extensive chemotherapy in an attempt to downstage patients from unresectable disease to resectable disease [20]. If tumours remain unresectable, thermal ablation and SBRT are a ‘last resort’ local curative intent treatment option with a presumed superior oncological outcome [3, 20].

The current primary efficacy rate of thermal ablation (complete ablation after the first procedure) for CRLM ≤ 3 cm (92–100%) is approaching to local recurrence rates after surgery for similar sized tumours [11, 29–32]. However, multiple studies have shown that efficacy significantly decreases to below 80% following thermal ablation of CRLM > 3 cm [11, 24, 33, 34]. For these larger-size tumours, novel MWA generation systems or tumour-bracketing multiprobe ablation techniques are preferred.As wide peri-ablational margins with > 5 mm margins, and if possible > 10 mm, are associated with technical success (A0 ablations), multiple electrodes may be used to increase the size of the ablation zone [35]. With the use of MWA, higher intra-tumoural temperatures, faster heating, shorter procedure times and larger ablation volumes with wider margins can be achieved, even in larger tumours [36–38]. Also, due to its active heating mechanism MWA might be less susceptible to the “heat-sink” effect of conductive heating with RFA [37].

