The 1- and 2-year local control rate for SBRT in multiple studies (all retrospective or prospective cohort studies) ranges from 50 to 95% and 45–92%, respectively [39–49]. Several studies showed that increased tumour size had a negative influence on the local control rate [43, 44, 50]. Even with increased tumour sizes, SBRT can be administered safely when a tumour is located in proximity to the gallbladder, bile ducts, main vessels and the diaphragm. No anaesthesia is required and recent advances in SBRT techniques seem to have reduced radiation induced toxicity. With this new magnetic resonance (MR)-guidance technique, the tumour is visualized during radiation delivery. Radiation can be delivered “gated” (i.e. beam-on only when the tumour is in the predetermined position) using small uncertainty margins and thereby limiting the dose delivered to normal organs, likely resulting in decreased toxicity [51, 52]. Nonetheless, major complications still occur in 0–9% and toxicity grade I-II occurs in 23–78% of patients [43, 50, 53–56].

Studies directly comparing thermal ablation to SBRT for intermediate-size CRLM are scarce. One recent study compared thermal ablation to SBRT for all sizes of unresectable CRLM, where results should be interpreted with caution, because of potential residual confounding due to non-randomized nature and selection bias [57]. The LTPFS and LC significantly improved in the thermal ablation group compared to the SBRT group for all sizes. In addition, stratification of results of intermediate size CRLM significantly favoured thermal ablation over SBRT. In this study, size of CRLM was a significant predictor for development of LTP in the thermal ablation group. Nonetheless, size of CRLM did not predict the development of LTP in the SBRT group. Therefore, it was suggested that SBRT might be less susceptible to larger tumour-sizes. In contrast, a recent propensity score-based comparison of LC favoured SBRT over thermal ablation for intermediate size CRLM [16]. We chose to allow for one re-ablation for local tumour progression if detected within 6 months. It would otherwise be unjust to compare an easily repeatable ablative method (MWA) to a treatment that is more difficult to repeat safely (SBRT).

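### The microwave arm alone has an early scan and an event-free completion ablation, on top of the 6-month exemption that both arms share; the primary endpoint needs a sensitivity analysis without retreatment credit

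*Protocol article*

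**What the plan says.** The Microwave Ablation section sets an early check: "To assess technical efficacy a ceCT (or ceMRI) should be made within two weeks after the procedure". Residual disease or an inadequate margin found on imaging may be treated by completion ablation up to 6 weeks after the first procedure. That first procedure is then recorded as technically unsuccessful, but "when successfully re-ablated the retreated residue will not count as an event for the primary endpoint LTPFS". The same section adds that an early recurrence successfully re-ablated within 6 months is not an event either.

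The Stereotactic Body Radiotherapy section describes no early efficacy scan and no completion step. It has the 6-month exemption for re-SBRT, without the condition that the retreatment succeeds. Outcome Measures states the 6-month exemption for both techniques and does require success. It also defines the secondary local control endpoint so that repeat treatment is allowed.

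Follow-Up says: "Follow-up imaging and laboratory tests will be identical in both treatment arms to avoid bias". The schedule itself is in Fig. 2, which is not available here. The Discussion describes the retreatment allowance this way: "We chose to allow for one re-ablation for local tumour progression if detected within 6 months".

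**The concern.** The primary comparison is between two techniques, so the rule for what counts as a local failure should work the same way in each arm or be declared as different. Here one arm has an additional look at the tumour and an additional retreatment that is not counted. A tumour could have residue completed at week 5, recur, be re-ablated before month 6, and still be a success at 12 months. An SBRT tumour has at most the second of these two exemptions.

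If this credit is material, a significant result could partly reflect the event rule, or a true SBRT advantage could be diluted. The endpoints named in the article would not separate these explanations, because both the primary endpoint and local control credit retreatment. An analysis of first local progression alone would not separate them either: the completed residue is labelled technical failure, not progression, so it would still pass as a success.

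**Working it through.** **Rules side by side**

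| Rule | MWA | SBRT |
|---|---|---|
| Efficacy scan within 2 weeks | yes | none described |
| Event-free completion up to 6 weeks, if successful | yes | none described |
| Event-free same-technique retreatment up to 6 months | yes, if successful | yes; success required in Outcome Measures, not stated in the SBRT section |

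The 6-week window lies inside the 6-month window. The part specific to MWA is therefore earlier detection, a possible second exemption for the same tumour, and completion for an inadequate margin where there is no recurrence.

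**The plan's own power figure.** Statistics states: "Group sample sizes of 33 in group 1 and 33 in group 2 achieve 81.059% power". Group 1 "is assumed to be 0.665 under the null hypothesis and 0.3350 under the alternative hypothesis", and group 2 is at 0.665. With a two-sided unpooled Z-test at 0.05:

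- standard error = √(0.335×0.665/33 + 0.665×0.335/33) = 0.1162
- power = Φ(0.33/0.1162 − 1.96) = 0.8106, which agrees with the plan.
- Exact binomial enumeration of the uncorrected chi-square test gives 0.8125.

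**An assumed net gain for MWA.** The Discussion gives one relevant figure: "multiple studies have shown that efficacy significantly decreases to below 80% following thermal ablation of CRLM > 3 cm". This suggests that about 20% or more of first procedures could be incomplete. Assume that 20% need completion and that 10–20% of those later recur and are successfully re-ablated by 6 months. The second exemption is then worth 0.20×0.10 = 0.02 to 0.20×0.20 = 0.04. I extend the range to 0.05 to allow something for earlier detection. The 10–20% and the extension are assumptions; neither is in the documents.

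**Effect on the test** (exact enumeration, 33 per arm, uncorrected chi-square at 5%, one observation per patient, no matching credit for SBRT). The middle columns take equal rates apart from the credit. The last column takes SBRT at 0.665 and MWA at 0.335 plus the gain.

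| Net MWA gain | P(significant for MWA), base 0.60 | base 0.665 | base 0.70 | Power for SBRT |
|---|---|---|---|---|
| 0 | 3.0% | 2.7% | 2.7% | 81.3% |
| 0.02 | 4.2% | 3.9% | 3.9% | 76.2% |
| 0.04 | 5.9% | 5.7% | 5.8% | 70.6% |
| 0.05 | 6.9% | 6.7% | 6.9% | 67.6% |

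The normal approximation at a gain of 0.05 gives a power of 66.0%, close to the exact figure.

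**The case against.** The strongest reply is that the trial compares strategies, not single procedures. The Introduction and Discussion call it unjust to judge an easily repeatable technique on one attempt, and Outcome Measures defines success as eradication at 12 months. A tumour eradicated after completion meets that definition. This stands, and it is why the primary definition need not change. It does not remove the value of showing how far a difference depends on a rule written for one arm only.

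Several stronger readings are tempting but not supported.

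- *Completion never counts as an event.* The exemption applies only if re-ablation succeeds; a failed completion is not exempted.
- *The bias is large.* A reader might take 20% of tumours as exempted and 90% of those as failures turned into successes, a gain of 0.20×0.90 = 0.18. The chance of a significant MWA win would then be 36% (0.78 versus 0.60) or 45% (0.88 versus 0.70). That arithmetic is right but the comparator is wrong: without the completion rule, most residue successfully re-ablated by week 6 would be exempt under the shared 6-month rule. The 80% figure also concerns thermal ablation in general, and a narrow margin is not a certain failure.
- *Follow-Up is contradicted outright.* The two-week scan is described as a technical-efficacy check, and Fig. 2 is not shown. The passages are in tension; more cannot be said.
- *The Discussion's single re-ablation is breached.* That allowance is for local progression, whereas completion treats residue. Whether both may apply to one tumour is left open.

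One wording difference runs the other way: the SBRT section omits the success condition. A separate analysis plan may also hold a suitable sensitivity analysis; the point is only that the article names none.

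**Conclusion.** The asymmetry is in the text, and the completion rule can favour only MWA. Its size is not in the documents. Under an assumed net gain of 2 to 5 points, the chance of a significant result favouring MWA rises from about 3% to about 4–7%, and the power to show an SBRT advantage at the design values falls from 81% to about 68–76%. These figures rest on the assumed gain, on one tumour per patient although the endpoint is per tumour, and on no matching credit for SBRT. This is a modest weakness that is cheap to cover. It does not show that the primary endpoint is invalid or that a false MWA win is likely.

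**What to change.** Keep the primary definition and add the following.

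1. Pre-specify a sensitivity analysis of 1-year LTPFS in which any local failure after the first treatment is an event in both arms: residual disease leading to completion ablation, or first local progression, regardless of retreatment. Residue must be named explicitly, because it is otherwise classed as technical failure.
2. Show separately the completions done only for an inadequate margin, since these are not established failures.
3. Report the number of completion ablations and the number of tumours that used both exemptions.
4. Reconcile the wording: the statement of identical imaging in Follow-Up with the MWA-only scan; whether both exemptions may apply to one tumour, in view of the Discussion; and the SBRT section with the success condition in Outcome Measures.

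The cost is one extra analysis and some text. The technical-failure grade is already required, so little new data should be needed, and patient care does not change. The downside is that the analysis may look less favourable to MWA. Because SBRT has no matching early scan, it must be read as a bound and not as an unbiased estimate.
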